### Relevant concomitant care permitted or prohibited during the trial {11d}

Participants can continue their neuropathic pain medication when the dosage has been stable for at least one month. Acetaminophen and non-steroid anti-inflammatory drugs are allowed as escape medication for acute pain other than the neuropathic pain due to CIAP. Oral phenytoin, opiates and other topical analgesics are not allowed. Use of escape medication will be recorded in the on a daily base.

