#### Secondary outcomes

All secondary outcomes are evaluated for phenytoin 20% versus 10% versus placebo cream in DOBRET positive, negative and all participants.

The change between baseline and week 2 for each intervention is assessed for:Pain intensity measured on theNRSNeuropathic Pain Symptom Inventory (NPSI), evaluating on the NRS neuropathic pain characteristics [27]NRS for the 3 worst pain characteristics≥30% and ≥50% improvement on the NRS compared to placebo within one participant, reflecting at least moderate and at least substantial improvement [28]Patient-reported percentage of pain reduction at the end of the second week of each interventionOnset of the analgesic effect after applicationDuration of the analgesic effect after one applicationDaily number of cream applicationsUse of escape pain medicationQuality of life measured on thesubscales of the Brief Pain Inventory (sBPI), evaluating on the NRS pain interference regarding general activity, mood, walking ability, normal work, relations with other people, sleep, and enjoyment of life [29]EQ5-5D-5L, measuring the health status on the visual analogue scale, and on a 5-point scale pain/discomfort, anxiety/depression, mobility, self-care and usual activities [30]Patient Global Impression of Change Scale (PGIC), measured on a 7-point scale [31]To evaluate the safety and tolerability of phenytoin 10% and 20% creamTolerability is defined as time-to-discontinuation of an assigned treatment since randomization.Safety is based on the safety assessments including physical examinations, clinical laboratory evaluations, vital signs and frequency of AEs or SAEs. (S)AEs will be categorized according to the Common Terminology Criteria for Adverse Events and will be rated for severity and association with the study drug.Detection of phenytoin in plasmaPredictive value of DOBRET in sustained pain reduction due to phenytoin creamTo evaluate the correlation between the PCS and the pain-reducing effect of topical phenytoin

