## Data collection and management

### Plans for assessment and collection of outcomes {18a}

Demographic data and baseline assessments will be collected through an electronic or paper questionnaire. Medical history and past and current analgesic use with its effects will be asked at baseline visit or extracted from the UMCU electronic medical records. At baseline, at the 14th day of each treatment period, 3, 6 and 12 months of the open-label extension self-administered questionnaires will be collected (see for types of questionnaires Table 1). In the 6-week double-blind period, the NRS and the use of escape medication will be queried every evening. Adverse events will be asked and registered at each visit after a treatment period, and in the questionnaires in the open-label extension at 3, 6 and 12 months. The electronic questionnaires are automatically locked after completion. Research physician will enter the paper questionnaires into the electronic system and will store the paper questionnaires for 15 years. After completion of the trial and filling in all paper questionnaires, the electronic database will be locked. The analysis of phenytoin plasma levels will be performed with state-of-the-art liquid chromatography–mass spectrometry.

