## Statistical methods

### Statistical methods for primary and secondary outcomes {20a}

Descriptive statistics will be used for baseline characteristics/demographics (age, sex, highest degree of education, country of birth, profession, duration and localization of pain, current neuropathic pain therapy, and past analgesic use), use of study creams (daily amount of use, number of daily applications, onset, duration and percentage of analgesic effect).

The primary endpoint measured on the NRS, as well as all other secondary endpoints, will be analysed according to the intention-to-treat (ITT) principle, incorporating all participants randomized irrespective of receiving treatment and having at least one efficacy measurement. For the primary analysis, the treatment effect will be determined in participants with a DOBRET-positive response at screening, evaluating the mean difference in NRS at week 2 between placebo and phenytoin 20% cream. Linear mixed-effects models (LME) will be used to account for the intra-individual clustering of observations. In brief, we will use an LME with fixed effects for time (week 1 or 2), treatment period (1 or 2 or 3), treatment (20% or 10% or placebo), the interaction between time and treatment, and NRS score at screening. The random part will be modelled with a random intercept and slope for time per individual, and an unstructured covariance matrix. The random slope for time will be kept in the model only if statistically significant. The likelihood ratio test will be used to test the significance of treatment; 95% confidence intervals will be based on the profile likelihood. Sensitivity analyses will be performed to evaluate (1) treatment-period interaction to assess potential carry-over effects and (2) per-protocol analysis involving all participants who completed the study. As secondary analysis, we will evaluate the treatment effect in all randomized patients irrespective of DOBRET, and explore the interaction between DOBRET outcome and treatment using additional interaction terms. Treatment effects on the NPSI, EQ-5D-5L, sBPI and PGIC will be evaluated in the same manner as the primary outcome.

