### Methods for additional analyses (e.g. subgroup analyses) {20b}

As an exploratory objective, we will determine the test accuracy for DOBRET to identify participants who benefited from treatment, where treatment benefit is defined as a 30% reduction from baseline NRS. The following factors will be tested in the models for confounding effects: pain duration, and intensity, use of co-medication and escape medication, pain characteristics, pain catastrophizing score, level of education and duration of effect of study medication. Linear regression analyses will be used to evaluate the correlation of pain reduction with pain duration, and intensity, use of co-medication and escape medication, pain characteristics, catastrophizing, level of education and duration of effect. For all analyses, results will be considered significant when *p* < 0.05. For the subgroup analysis, we will correct the *p*-value according to Bonferroni.

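### Duration of effect of the cream and on-treatment escape medication are listed as candidate confounders in the additional (DOBRET-related) models, although both are post-randomisation outcomes

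*Protocol article*

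**What the plan says.** The protocol article's section on additional analyses {20b} opens with the DOBRET accuracy objective: "As an exploratory objective, we will determine the test accuracy for DOBRET to identify participants who benefited from treatment". The next sentence gives the list at issue: "The following factors will be tested in the models for confounding effects: pain duration, and intensity, use of co-medication and escape medication". After pain characteristics, the list closes with "pain catastrophizing score, level of education and duration of effect of study medication". A further sentence plans linear regressions of pain reduction on largely the same factors.

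The Secondary outcomes section includes both the duration of analgesia after an application and the use of escape medication. It says of everything listed there: "All secondary outcomes are evaluated for phenytoin 20% versus 10% versus placebo cream in DOBRET positive, negative and all participants".

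On timing, the data collection section {18a} states: "In the 6-week double-blind period, the NRS and the use of escape medication will be queried every evening". On purpose, the concomitant care section {11d} says that acetaminophen and non-steroid anti-inflammatory drugs are "allowed as escape medication for acute pain other than the neuropathic pain due to CIAP".

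The primary analysis is set out separately in {20a}. Its mixed model has "fixed effects for time (week 1 or 2), treatment period (1 or 2 or 3), treatment (20% or 10% or placebo", followed by the time-by-treatment interaction and the screening NRS.

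**The concern.** A confounder is a prior common cause of the exposure and the outcome. A variable that the exposure brings about, or that is one face of the outcome, does not qualify. Adjusting for it changes the quantity estimated from a total association to what is left once part of the response is held fixed. If the variable also shares unmeasured causes with pain, adjustment can add bias of its own.

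Testing first does not guard against this. Neither a significance test nor a change-in-estimate rule can tell a confounder from a consequence, and both tend to keep the variable most closely tied to relief, which is where the harm is greatest.

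At stake is the main secondary objective: whether DOBRET identifies people who will have sustained relief. The test records an early response to phenytoin 10% cream before the first period, whereas duration of effect is a later measure of response to the cream. Holding it fixed removes part of what DOBRET is meant to predict, and it is not known when the test is performed.

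**Working it through.** No figure stated in the protocol enters this point, so there is none to reproduce. The check is to place each variable in time and role, and then to see what adjustment would do.

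**Duration of effect.**
- Role: secondary outcome, compared across creams (Secondary outcomes). Section {20a} summarises it together with onset and percentage of analgesic effect, so it describes the response.
- Timing: it cannot exist before a cream has been applied.
- Path: under {6b} and {11a}, how often the cream is applied each day follows from how long its effect lasts. Duration therefore lies between the assigned cream and the pain score.
- Conclusion: it follows both the DOBRET result and the cream, and can confound neither.

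**Escape medication.**
- Role: secondary outcome, compared across creams.
- Timing: recorded each evening of the double-blind phase ({18a}).
- Path: less clear, because {11d} restricts it to other pain. Two mechanisms pull in opposite directions for a comparison of creams. If placebo periods prompt more use and that use lowers the NRS, the unadjusted difference is narrowed and adjustment widens it. If use only marks worse pain, adjustment shrinks the difference.
- Conclusion: not a baseline confounder, but the direction of any distortion is open.

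**Other listed factors.** Pain duration, education and, if taken at baseline, intensity, pain characteristics, catastrophizing and co-medication precede treatment. DOBRET status is not randomised, so these can confound its association with relief. For a comparison of creams within a participant they are constant across periods; there they can predict or modify the effect but not confound it.

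**Illustration for duration of effect (assumed values).** Let X be the DOBRET result, Y the relief under phenytoin cream, δ the difference in mean Y between DOBRET groups, and D the duration. Assume D = kY + u with k > 0 and u independent of X and Y. Let r be the correlation of D with Y among participants with the same DOBRET result.

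- Slope of Y on D at fixed X: b = k·Var(Y|X) / [k²·Var(Y|X) + Var(u)].
- D differs between DOBRET groups by kδ.
- Adjusted coefficient of X: δ − b·kδ = δ(1 − r²), because r² = k²·Var(Y|X) / [k²·Var(Y|X) + Var(u)].

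| Assumed r | 1 − r² | Share of δ left |
|---|---|---|
| 0.3 | 1 − 0.09 | 91% |
| 0.5 | 1 − 0.25 | 75% |
| 0.7 | 1 − 0.49 | 51% |

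The document gives no value for r, so the table shows direction and a possible range, not an estimate. It applies only to duration of effect.

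**The case against.** The strongest reply is about scope. The sentence sits under additional analyses, directly after an exploratory objective, and does not say which models it means. A reader might infer that the planned 2-point difference between phenytoin 20% and placebo cream is at risk. The same algebra would turn it into 2 × 0.91 = 1.82, 2 × 0.75 = 1.50 or 2 × 0.51 = 1.02 points. The document does not support that reading: the primary model's terms are fixed in {20a}, and neither variable is among them. This part of the reply stands in full.

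Second, being tested is not being retained. The article gives no retention rule, and a fuller plan may supply one. That stands too: the harm is conditional on a model keeping the term.

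Third, escape medication is allowed only for other pain. A reader might infer that adjusting for it must pull effects towards zero. The permitted use makes the link to the cream uncertain, and the sign could go either way. Being listed as an outcome does not show that the cream affects it.

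Fourth, the separate regressions of pain reduction on these factors are descriptive and not an error. With duration of effect as a predictor, however, such a regression is close to circular, since someone without relief has no duration to report. It should not be read as explaining relief.

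None of this makes either variable a confounder.

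**Conclusion.** The point holds in a limited form. The protocol names as candidate confounders two variables that it elsewhere defines as outcomes of each cream. The case is firm for duration of effect: a DOBRET model that retains it over-adjusts and could understate how well the test predicts sustained relief. For on-treatment escape use the principle is the same, but the evidence is weaker and the direction unknown.

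The primary result is not affected. The size of the bias cannot be computed from the document; the 91% to 51% range rests on the assumed linear relation and on assumed correlations of 0.3 to 0.7. The conclusion also takes the models in {20b} to be chiefly those relating DOBRET to relief, as the order of the sentences suggests. This is a correction of wording in secondary and exploratory analyses, worth making because DOBRET is the main secondary objective.

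**What to change.** In {20b}:

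1. Remove duration of effect of the study cream and on-treatment escape medication from the list of factors tested for confounding.
2. State that confounder adjustment uses only variables measured before the first treatment period, and that it applies to the between-participant association of DOBRET with relief.
3. State that in within-participant comparisons of the creams the same baseline variables serve only as predictors or effect modifiers (interaction with treatment).
4. Report duration of effect and escape use as outcomes by cream, as the Secondary outcomes section already intends, and label any regression of pain reduction on them as descriptive.

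The cost is a few lines of text. No data collection, sample size or primary analysis changes.

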### Eligibility criteria {10}

Patients will be recruited from the UMCU neurology outpatient clinic. When patients from outside of the UMCU want to participate, a consultation for the confirmatory diagnosis will be carried out. Inclusion criteria are age ≥ 40 years; confirmed CIAP diagnosis [25]; presence of ≥3 months localized neuropathic pain in two symmetrical areas of feet/lower legs; with a pain intensity difference of ≤1 point on the NRS; ≥1 h daily pain; with a weekly mean pain score between ≥4 and <10 on the NRS at study entry; Douleur Neuropathique 4 questions (DN4) score ≥4 [26]; and no changes in neuropathic pain medication of ≥1 month. The main exclusion criteria are other (neuropathic) pain conditions; open wounds in the neuropathic pain area; current use of topical analgesics; hypersensitivity to study drugs; oral use of phenytoin and (planned) pregnancy. The primary investigator ([name]) and the two research physicians ([name] and [name]) will screen patients for eligibility. Eligible patients who are willing to participate will be recruited for the trial.

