### Sample size {14}

We hypothesized a mean difference of 2 points on the NRS between placebo and the 20% cream (π1), and a mean difference of 1 point between 20% and 10% cream (π2). Based on preliminary data [21], we assumed for both treatment effects a standard deviation of 3.3 (standardized effect sizes: π1 = 0.61, π2 = 0.30). Using the same dataset, we conservatively assumed a correlation between NRS scores within participants (intraclass correlation) of 0.3. Seven participants per sequence (e.g. placebo–20%–10%, or 10%–placebo–20%) would be required to achieve 80% power and a two-sided significance level of 5% (= 7 × 6 sequences = 42 total sample size) [32]. Assuming a 10% drop-out rate, we will enrol 8 responding participants per group or 48 in total. DOBRET-negative participants are assumed to exhibit a mean difference of 1.5 point s (SD 4) on the NRS between placebo and the 20% cream, where 1 in 3 patients are assumed to be DOBRET-negative. This would result in a pooled overall treatment effect across DOBRET negative and positive participants of 1.83 (SD 4). Enrolling 24 DOBRET-negative and 48 DOBRET-positive participants would result in a power of 84% for the overall population.

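### As most naturally read, the exploratory regression of pain reduction on pain intensity has baseline pain on both sides, so a slope of zero is the wrong null for whether phenytoin's effect depends on pain intensity

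*Protocol article*

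**What the plan says.** Methods for additional analyses {20b} states that "Linear regression analyses will be used to evaluate the correlation of pain reduction with pain duration, and intensity", followed by co-medication, escape medication, pain characteristics, catastrophizing, education and duration of effect. The threshold is general: "For all analyses, results will be considered significant when" p is below 0.05. Bonferroni is named only for subgroups ("For the subgroup analysis, we will correct the" p-value).

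The regression sentence defines neither reduction nor intensity. Earlier in the same section, benefit is a drop measured from baseline: "where treatment benefit is defined as a 30% reduction from baseline NRS". The Secondary outcomes list opens with "The change between baseline and week 2 for each intervention is assessed for", and pain intensity on the NRS is its first item. That list also includes the correlation between the PCS and phenytoin's pain-reducing effect.

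The mixed model in Statistical methods {20a} adjusts for the screening NRS. It plans to explore a DOBRET-by-treatment interaction, but it names no interaction of treatment with pain intensity.

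**The concern.** Intensity sits in a list with pain duration and education, so it is naturally read as baseline pain. Reduction is naturally read as baseline minus week 2. Regressing the second on the first builds a positive slope into the analysis, because a high baseline score raises both sides and tends to be followed by a lower score whatever cream is used. A zero slope would then mean that scores repeat perfectly from baseline to week 2. It would not mean that phenytoin works equally well at all pain levels.

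At stake is a reported finding that phenytoin works better in patients with more pain when the data show only regression to the mean. If the true effect were smaller at higher pain, the sign could even be reversed.

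**Working it through.** **Inputs from the protocol article.** Sample size {14}: "we assumed for both treatment effects a standard deviation of 3.3" and "we conservatively assumed a correlation between NRS scores within participants (intraclass correlation) of 0.3"; 48 DOBRET-positive participants and 72 overall. Eligibility criteria {10}: "with a weekly mean pain score between ≥4 and <10 on the NRS at study entry".

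**Inputs assumed here.** Mean pain 6 to 6.5 before selection; SD 1.5 to 3.3; baseline-to-week 2 correlation r from 0.3 to 0.8; normal scores.

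**The plan's own figure.** Take 3.3 as the SD of NRS scores, 0.3 as the correlation between two scores of one participant, and means 0, 1 and 2 for placebo, 10% and 20%. The squared deviations sum to 2, and the non-centrality for the 2-df treatment test is n × 2 / (3.3² × 0.7) = 2n / 7.623.
- n = 36: 9.45, power 79.2%.
- n = 42: 11.02, power 85.3%.

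So 42 is the smallest multiple of six above 80%, and 42 / 0.9 = 46.7, rounded up to 48. The stated figures reproduce under this use of SD and correlation.

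**Slope when the effect is zero or constant.** Let B be baseline and F week 2.

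slope = cov(B − F, B) / var(B) = 1 − r × SD(F)/SD(B)

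With equal SDs this is 1 − r: 0.7 at r = 0.3 and 0.2 at r = 0.8. A constant effect shifts the intercept only.

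**Rejection of slope 0 without the entry window.** corr(B − F, B) = √((1 − r)/2).
- r = 0.3: 0.592. Fisher z: atanh(0.592) × √45 − 1.96 = 2.6, so 99.5% at n = 48.
- r = 0.8: 0.316, so 59%.

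**Effect of the entry window.** Selecting on the predictor leaves the slope at 0.7 but narrows the baseline SD from 3.3 to 1.61. The residual SD is 3.3 × √(1 − 0.09) = 3.15. The correlation becomes 0.7 × 1.61 / √(1.127² + 3.15²) = 0.34, and simulated rejection at n = 48 falls to 67%. The window therefore lowers the false-positive rate. Bounding follow-up scores at 0 to 10 reduces their spread and brings it back to about 83%.

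**Simulated rejection at n = 48, no phenytoin effect, entry 4 to <10, bounded scores:**

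| SD (mean) | r = 0.3 | r = 0.5 | r = 0.7 | r = 0.8 |
|---|---|---|---|---|
| 3.3 (6) | 83% | 66% | 46% | 32% |
| 2.0 (6) | 95% | 84% | 57% | 41% |
| 1.5 (6.5) | 99% | 92% | 69% | 51% |

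Further results at SD 3.3, r = 0.3, bounded:
- n = 72: about 95%.
- Constant 2-point effect: about 81% (n = 48) and 94% (n = 72).
- Placebo reduction regressed on baseline: about 84% and 95%, as high as for phenytoin.
- Bonferroni over seven factors: about 57% and 81%. The sentence lists eight, which changes little.

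Without bounding, at SD 3.3 and r = 0.8, rejection is about 20%.

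**Placebo-minus-phenytoin week 2 difference regressed on baseline:** 4 to 6% across the same settings.

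**Wrong sign.** If the effect falls by 0.3 points per point of baseline pain, the planned slope is 0.7 − 0.3 = +0.4. It is significantly positive in about 28 to 29% of trials (SD 3.3, r = 0.3, unbounded).

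**Spill-over.** For a factor correlated 0.3 with baseline (assumed), n = 48: about 7 to 20% if baseline is not in the model, and about 4 to 6% if it is. With baseline in the model, the other coefficients are algebraically the same up to sign for change and for follow-up score.

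**The case against.** The strongest objection is that the sentence says neither from baseline nor baseline intensity. The secondary outcomes also contain a within-participant comparison with placebo (the 30% and 50% improvement items) and refer to phenytoin's own pain-reducing effect. If reduction means the contrast with placebo, the test is sound at about 5%. An article may also leave the dependent variable of an exploratory regression to the fuller document. This stands as a limit on certainty. It does not remove the point: the only definition of reduction in that section is from baseline, and the article itself fixes the method, the predictors and the threshold. Reading reduction as a percentage does not help: with no effect, rejection at n = 48 and r = 0.3 is still 56 to 98%.

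The size also depends on figures the protocol does not give. The 0.3 is described as conservative and is not stated to be a baseline-to-follow-up correlation. The 3.3 is stated for treatment effects. Both objections stand, which is why a range is shown.

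A reader might infer more than the documents support:
- That most trials would falsely reject whatever the correlation. At r = 0.8 they would not.
- That the entry threshold makes the test worse. It leaves the slope unchanged and lowers rejection.
- That the PCS result is invalidated in the same way. The spill-over is modest, and nearly nil if baseline is in the model, which the planned testing of factors for confounding leaves open.
- That this undermines the personalised-medicine aim. The Objectives tie that aim to DOBRET, not to these regressions.

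**Conclusion.** The point holds on the natural reading of {20b} and the Secondary outcomes. Testing slope 0 for change from baseline against baseline intensity does not answer whether phenytoin's effect depends on pain intensity. With an assumed mean of 6 to 6.5, SD 1.5 to 3.3, the entry window and bounded scores, false rejection at n = 48 is about 83 to 99% if r = 0.3 and about 30 to 50% if r = 0.8, against a nominal 5%. The same association would appear for placebo, so it cannot be attributed to phenytoin.

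The damage is mainly to one factor, intensity, in an exploratory analysis. The primary comparison of phenytoin 20% with placebo and the DOBRET-by-treatment interaction are not touched. The text should be corrected, but it does not threaten the trial's main conclusion.

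**What to change.** In {20b}, and for the PCS outcome under Secondary outcomes, state that the dependent variable for baseline factors is the within-participant difference in 7-day average NRS over week 2: placebo minus phenytoin 20%, and placebo minus phenytoin 10%. State that baseline intensity will not be tested against change from baseline.

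Alternatively, test treatment-by-factor interactions for week 2 in the {20a} mixed model. Because that model already has a time-by-treatment term, this needs the factor-by-treatment-by-time term or a model of week 2 only. A plain treatment-by-factor term is not the same analysis.

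Report escape medication and duration of effect descriptively. They arise during treatment and cannot serve as baseline effect modifiers.

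The cost is a wording change and no new data, since every participant is scheduled for a placebo period. The difference of two periods is noisier. Its residual variance given baseline is 2 × SD² × (1 − r), against SD² × (1 − r²) for the change score, a ratio of 2/(1 + r). That is 1.54 at r = 0.3 (residual SD 24% larger) and 1.11 at r = 0.8 (5% larger). Participants missing one of the two week 2 scores drop out of the simple regression, but not out of the mixed model.
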